## **1.6 STUDY OBJECTIVES and related endpoints**

The study is designed to estimate the effect of intravenously administered Butylscopolamine bromide on the duration of labor. Outcomes also include labor pain, use of oxytocin augmentation, mode of delivery, and a validated questionnaire on birth experience one month after delivery.

### **1.7 Primary Endpoint**

#### **Primary endpoint:**

Duration of labor from the time when the participant was given IMP to delivery

#### **Secondary Endpoints:**

##### *Endpoints regarding labor:*

Duration from when the participant was given IMP, to 10 cm dilatation (time to event variable).

Mean cervical dilatation rate, calculated as mean cervical dilatation from IMP is given to 10 cm (continuous variable)

Duration of labor from the onset of active labor (at least 3 cm dilatation) to delivery (time to event variable)

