### **Cervical dilatation**

Will be examined immediately before randomization (after the woman has crossed the alert line of the partogram), when IMP is given (if there is more than 45 minutes between randomization and IMP). After IMP is given the midwife will examine the cervix according to ward routine, but at least every two hours.

**Questionnaire** Childbirth experience questionnaire (CEQ) developed and validated in Sweden consists of 22 items in 4 categories: own capacity, professional support, perceived safety and participation. We have added one question concerning request for caesarean section in next pregnancy

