## **6 ASSESSMENTS**

### **6.1 Assessment of Efficacy Response**

The following parameters will be recorded:

Duration of labor from the time when the participant was given IMP to delivery

Duration of labor from the onset of active labor (at least 3 cm dilatation) to delivery

Duration of the active phase of first stage of labor (at least 3 cm dilatation), from the time when it was noticed that the alert-line of the partogram was crossed (between 3 cm and 9 cm dilatation) and the participant was given IMP, to 10 cm dilatation, or emergency cesarean delivery.

Mode of delivery – spontaneous vaginal delivery, vacuum delivery, forceps delivery, emergency cesarean delivery

Indication for operative delivery

Amount of oxytocin given measured as

1. total time with treatment

2. International Units (IU) (the midwife measures mL of oxytocin solution given during labor. IU are calculated based on standardized concentration of the infusion solution [10 IU oxytocin in 1000 mL NaCl solution])

Apgar score at 5 minutes and 10 minutes after delivery

Admission to the Neonatal Intensive Care Unit

Pain scores using a Visual Analogue Scale at baseline and 30 minutes after administration of IMP

Birth experience measured by the validated questionnaire Child Birth Experience Questionnaire

Maternal heart rate – continuous registration at least 30minutes from administration of IMP

Fetal heart rate - continuous registration at least 30minutes from administration of IMP

Urinary retention

Anal sphincter injury

Postpartum hemorrhage

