A methodological issue is that while both the articles we use as a basis for the sample calculations report means and SDs for the duration of labor, this outcome is a time-to-event outcome, with emergency cesarean delivery as a censoring event. The primary outcome will be treated as such in the analyses, and this should also be reflected in the power calculation. However, background data on our primary endpoint are hard to find, and we have therefore based our sample size calculation on the results from Dencker et al.

In the study population, the expected proportion of emergency cesarean delivery will be approximately 7%. Hence, most (approximately 93%) duration times will be observed, and a sample size based on a traditional continuous outcome e.g. a two-sample t-test will give a good indication for the sample size. Due to the inherent skewness of labor duration data, one can expect published values of SD to be slightly overestimated.

With the SD of 2.8 given in Dencker et al., and a power of 80 % we would need in total 246 women (123 women in each group) to discover a difference of 60 minutes. Furthermore, we calculate that

we will need written informed consent from at least 600 women to be able to randomize approximately 250 participants (8% [50 women] will be lost because of elective cesarean section, 25% [140 women] will be induced or receive oxytocin before 3 cm, and 40% [165 women] will not cross the alert line). In addition some of the eligible women will not be randomized because the midwife on duty forget to take the necessary steps and some participants will withdraw from the study.

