### 9.3 Population for Analysis

The following populations will be considered for the analyses:

- Intention to treat (ITT) population: All randomized participants, regardless of protocol adherence.
- Per-protocol population (PP): Includes all participants who have followed the protocol, i.e. one dose of the study medication (IMP). Randomized patients who were not eligible are excluded.
- Safety population: Includes all participants who have received one dose of study medication IMP. Participants who withdraw from the study will be included in the safety analysis. A list of withdrawn participants, preferably with the reasons for withdrawal, will be made.

The primary population is the ITT population.

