### 9.5.1 Primary analysis

This protocol is designed to address a single primary endpoint, which is the duration of labor from when the participant was given IMP, to delivery

This is a time-to-event outcome, where vaginal delivery is the event of interest and emergency cesarean delivery is the censoring event.

The study is designed to establish the superiority of intravenously administered Butylscopolamine bromide compared to placebo on a single primary endpoint; the duration of labor from when the participant was given IMP, to delivery. The null hypothesis is that there is no difference in the duration of labor from when the participant was given IMP, to delivery, between the two treatment groups.

The alternative hypothesis is that there is a difference in the duration of labor from when the participant was given IMP, to delivery, between the two treatment groups.

Superiority of Butylscopolamine bromide on the duration of labor from when the participant was given IMP, to delivery, is claimed if the primary null hypothesis is rejected, and the group difference is in favor of Butylscopolamine bromide.

Statistical significance is claimed if the null hypothesis is rejected on the significance level (alpha) of 0.05 (two-sided). That is, if the p-value of the null hypothesis test is less than or equal to 0.05.

As there is only one identified primary analysis, there will be no adjustments for multiple testing in the secondary analyses. Secondary analyses on secondary endpoints will be regarded as supportive.

The primary endpoint will be analyzed using Weibull regression, and the p-value for the statistical hypothesis test for the primary endpoint will be the p-value from this analysis. Unadjusted Kaplan-Meier plots will be presented. The effect measures will include median (and quartiles) duration in the two treatment groups, and the proportion of women who give birth within 2, 4, 6, 8, 10 and 12

hours after randomization. All efficacy analyses will be presented by the size (point estimate) of the difference between the treatments and the associated 95% confidence interval.

The statistical analyses will be done in SPSS v23, or R version 3.5.0 (<https://www.r-project.org/>).

Robustness of the results will be checked using Cox regression, by including baseline characteristics known to be associated with labor duration as covariates, and performing the analyses with different options for data imputation.

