### **9.5.2 Secondary analyses**

Secondary endpoints in this study contain

1. Time-to-event variables (duration of labor from the time when the participant was given IMP to 10 cm dilatation, and duration of labor from the onset of active labor (at least 3 cm dilatation) to delivery,
2. Continuous variables (mean cervical dilatation, amount of oxytocin given, pain scores on VAS scales, pH values from umbilical artery and vein, postpartum hemorrhage and responses to CEQ),
3. Categorical or discrete variables (mode of delivery, admission to Neonatal Intensive Care Unit, urinary retention, anal sphincter injuries and Apgar scores).

Time-to-event variables will be analyzed as the primary endpoint.

Continuous and categorical variables will be analyzed by simple bivariate analyses (t-test, Mann-Whitney test or Pearson chi square test, as appropriate), with linear or logistic regression as robustness analyses.

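### The mean dilatation rate is defined only up to 10 cm, so women with a first-stage cesarean have no value and the comparison is restricted to a group selected after randomization

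*Protocol*

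**What the plan says.** The synopsis and Protocol 1.7 (Secondary Endpoints) define the endpoint as "Mean cervical dilatation rate, calculated as mean cervical dilatation from IMP is given to 10 cm (continuous variable"). Section 9.5.2 places it among the "Continuous variables (mean cervical dilatation, amount of oxytocin given, pain scores on VAS scales" and others), and states: "Continuous and categorical variables will be analyzed by simple bivariate analyses (t-test, Mann-Whitney test or Pearson chi square test, as appropriate"). Regression models serve there only as a check of robustness. None of these methods handles censoring.

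The protocol does provide for cesarean elsewhere:

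- Section 9.5.1, primary endpoint: "vaginal delivery is the event of interest and emergency cesarean delivery is the censoring event". Section 9.5.2 analyzes the time-to-event secondary endpoints, including time from IMP to 10 cm, in the same way.
- Section 6.1, duration of the first stage: the interval runs "to 10 cm dilatation, or emergency cesarean delivery".

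No such provision is given for the rate. The primary population in section 9.3 is ITT: "All randomized participants, regardless of protocol adherence". On data collection, section 5.2 (Cervical dilatation) says: "After IMP is given the midwife will examine the cervix according to ward routine, but at least every two hours".

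**The concern.** The rate needs an observed end at 10 cm. A woman delivered by cesarean in first stage never has one, so the endpoint cannot be computed for the full ITT population. Whether a woman reaches 10 cm is decided after randomization and is related to the outcome. Protocol 1.5 reports 15% cesarean among women who crossed the alert line against 2% among those with normal progress. Treatment may also affect it, since mode of delivery is itself a secondary endpoint.

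A test among women who reach 10 cm therefore compares two groups that randomization no longer protects. If the drug speeds dilatation and so averts some first-stage sections, its arm keeps slow women whose counterparts on placebo drop out. The protocol expects the drug to act in the first stage and not the second (1.5), so this endpoint lies close to the expected effect.

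**Working it through.** **Plan's own figure.** The protocol gives no figure for this endpoint. Its sample size concerns the primary endpoint and reproduces: 2 × [2.8 × (1.960 + 0.842) / 1]² = 123.07 per arm, against the stated 123 (246 in total). This point does not affect it.

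**Women without a value.** Number = 250 × cesarean rate × share of cesareans done in first stage.

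- Planning rate (9.1): "the expected proportion of emergency cesarean delivery will be approximately 7"%.
- Department rate in women crossing the alert line (1.5): 15%.
- First-stage share: not given; 25% to 100% assumed.

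| Cesarean rate | 25% | 50% | 75% | 100% |
|---|---|---|---|---|
| 7% | 4.4 | 8.8 | 13.1 | 17.5 |
| 15% | 9.4 | 18.8 | 28.1 | 37.5 |

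That is about 4 to 18 women (1.8% to 7%) at the planning rate and about 9 to 38 (3.8% to 15%) at the department rate. The protocol does not reconcile the two rates.

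**Effect within one arm, worst case.** Assume log-normal rates with log SD s = 0.5, and suppose every section falls exactly in the slowest fraction p. The mean among those kept, relative to the full mean, is Φ(s − z_p)/(1 − p), where z_p is the p-quantile of the standard normal:

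- p = 5%: 1.036
- p = 10%: 1.070
- p = 15%: 1.103

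Inflation that is equal in both arms does not create a difference where none exists.

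**Effect on the between-arm difference.** A simulation used a median of 1 cm/h, log SD 0.5 and 2,000,000 women per arm. The drug shifted the log rate by 0, 0.2 or 0.3. Section depended on speed sharply (perfect truncation), gradually (logistic, slope 2 per SD) or not at all. The last two columns give the completers' difference as a fraction of the true difference, over shifts of 0.2 and 0.3.

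| Dropped on placebo | Sharp | Gradual |
|---|---|---|
| 3.5% (7% × 50%) | 0.94–0.95 | 0.97 |
| 7% (7% × 100%) | 0.90–0.91 | 0.95 |
| 15% (15% × 100%) | 0.83–0.84 | 0.91–0.92 |

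The true benefit is understated by about 3% to 17%. The top of that range needs the 15% cesarean rate, every section in first stage, and perfect truncation. With a shift of 0 the difference is unbiased. With section unrelated to speed and equal between arms, the ratio is 1.00.

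**Scale against sampling error.** The coefficient of variation is √(e^0.25 − 1) = 0.533. The standard error of the relative difference at 125 per arm is 0.533 × √(2/125) = 6.7%. If the arms lost 10% and 5% with identical underlying speed, perfect truncation would shift the comparison by 1.070 − 1.036 = 0.034, half a standard error. With 3.5% against 1.5% lost, the shift is 1.4%, about 0.2 of a standard error. If section correlates only 0.5 with speed, these become 1.9% and 0.9%.

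**The case against.** The strongest reply is that the protocol never says these women are excluded. ITT is primary, and section 9.5 leaves full detail to a separate SAP, which is not available here. That SAP may contain a rule; under Mann-Whitney, for example, women not reaching 10 cm could be ranked lowest. It is fair to say that exclusion is a consequence of the definition and not a stated intention. But the definition is in the protocol and ends at 10 cm, so any such rule has to go beyond it.

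Four stronger readings are tempting, and the protocol does not support them:

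- *The women lost are the slowest.* The 15% against 2% is an association. Section 1.8 lists fetal distress and other indications beside dystocia, so these women tend to be slow but need not be the slowest.
- *The serial examinations are wasted.* Section 1.8 includes dilatation rate as a function of time among the exploratory endpoints, and this is not tied to 10 cm. It is only a partial remedy, because section 9.5.4 treats exploratory analyses as post-hoc.
- *The first-stage question goes unanswered.* Time from IMP to 10 cm is a secondary endpoint and keeps these women by censoring them at cesarean.
- *A sizeable spurious difference is likely.* A 5-point gap in first-stage sections between arms has no basis in the protocol and is large against a 7% total. Most plausibly the error is conservative.

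**Conclusion.** The point stands in limited form. As written, the definition and the test give a comparison restricted by a post-randomization event, affecting between about 4 and 38 of 250 women, depending on the cesarean rate and the unknown first-stage share. The between-arm bias is nil if the drug changes neither dilatation nor section. Otherwise it is modest and most likely hides benefit, at roughly 3% to 17% of the true difference. That range rests on an assumed log-normal rate, an assumed log SD of 0.5 and assumed links between speed and section.

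A reader might infer a threat to the trial's main conclusion. There is none: this is one supportive secondary endpoint, and the primary endpoint, the sample size and the time-to-10-cm analysis are untouched. The change is worth making because the better analysis needs no new data.

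**What to change.** Estimate the rate with a linear mixed model on all cervical examinations from IMP to 10 cm, or to the last examination before cesarean. Include baseline dilatation and random slopes, take treatment-by-time as the effect, and check for non-linear dilatation. Include all randomized women who have an IMP time; a woman never given IMP has no starting point and should be counted and reported. Report by arm the number not reaching 10 cm. The simple rate among women who reach 10 cm can stay as a descriptive figure.

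A crude rate of last minus baseline dilatation over elapsed time is a weaker substitute. It compares unequal stretches of labor and assumes that dilatation is linear.

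The cost is a revised endpoint definition in the protocol, matching SAP text, and a slightly more complex model for one supportive endpoint. The 7% and 15% cesarean figures should be reconciled at the same time, since they determine how many women are affected.

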#### **Mode of delivery:**

1. Spontaneous vaginal delivery vs operative delivery (vacuum, forceps or cesarean delivery) (dichotomous variable)
2. Vaginal delivery vs cesarean delivery (dichotomous variable)
3. Spontaneous vaginal delivery, vacuum delivery, forceps delivery, or emergency cesarean delivery (nominal variables)

#### **Amount of oxytocin given, measured**

1. As total time with treatment (continuous variable)
2. As International Units (IU). The midwife measures mL of oxytocin solution given

during labor. IU are calculated based on standardized concentration of the infusion solution [10 IU oxytocin in 1000 mL NaCl solution] (continuous variable).

Pain scores using a Visual Analogue Scale at baseline and 30 minutes after administration of each dose of IMP (continuous variable)

Postpartum hemorrhage (continuous variable)

Urinary retention, defined as need for urinary catheter before the participants leave the delivery ward (categorical variable)

Anal sphincter injury (categorical variable)

*Endpoints regarding the infant:*

Apgar score at 5 minutes and 10 minutes after delivery (ordinal variables)

pH levels in umbilical vein and artery after delivery (continuous variables)

Admission to the Neonatal Intensive Care Unit (categorical variable)

*Postpartum endpoints:*

Birth experience measured by the validated questionnaire Child Birth Experience Questionnaire (continuous variables for each sub category)

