## 1.2 Background - Therapeutic Information

When progress in labor is too slow, augmentation with oxytocin is commonly used to increase contractions (5). However, oxytocin has side effects. Administration of the drug, commonly by continuous intravenously infusion, is usually accompanied by continuous fetal heart monitoring and frequently by epidural analgesia, all decreasing a woman's ability to move. Augmentation with oxytocin is associated with an increased risk of fetal asphyxia (6-8), operative delivery and a negative birth experience (8-10). Oxytocin has been described as the drug most commonly related to preventable adverse events during labor and has a very unpredictable therapeutic index (11). A significant association has been shown between augmentation with oxytocin in first labor and anal sphincter injuries (12), post-partum urinary retention (13), postpartum hemorrhage (14) and delayed initiation of breastfeeding (15). Given that there is uncertainty regarding the efficacy of oxytocin, and that the use of oxytocin has considerable side effects, there is a need to evaluate alternative or adjuvant treatments for slow progress in the first stage of spontaneous labor.

Studies of the prevalence of augmentation with oxytocin report a high and increasing use of this drug, especially among first time mothers (9, 16, 17). A study of all Norwegian delivery units found a prevalence of oxytocin augmentation in primiparous women in spontaneous labor at term, with a single fetus in cephalic presentation (Robson group 1) from 44 to 48% in the years 2000-2011 (18). Data from Oslo University Hospital, Rikshospitalet, 2014-2015, show that 54% of women in Robson group 1 received oxytocin for augmentation of labor ((19)).

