Maternal: Common ( $\geq 1/100$  to  $< 1/10$ ): Gastrointestinal: Dryness in the mouth. Cardiology: Tachycardia, dizziness. Ophtalmology: Accomodation disturbance. Unknown frequency: Cardiology: Hypotension, flushing. Skin: Dyshidrosis. Immune system: Anaphylactic shock, anaphylactic reactions, dyspnea, skin reactions including urticarial, rash, erythema and itching. Other forms of hypersensitivity. Kidney: Urinary retention. Ophtalmology: Mydriasis, increased intraocular pressure. Rare cases with serious skin reactions like Steven-Johnsons syndrome have been reported.

According to WHO recommendations for augmentation of labor based on the Cochrane review from 2013 (22),(31), there are 5 RCTs comparing Buscopan with placebo including altogether 845 newborns with no differences in transfer to the Neonatal Intensive Care Unit. One RCT with 100 fetuses did not show any differences in prevalence of fetal distress. One RCT with 130 fetuses did not show any difference in fetal bradycardia, and two RCTs with 230 fetuses did not show any difference in fetal tachycardia. None of the 17 RCTs in the Cochrane review reported any side effects related to Buscopan (22).

Women who are allocated to the control group will contribute to answer an important medical question for future laboring women and their children. They will need an IV access, which could be considered a down side. However, it is routine procedure in the hospital to establish an IV line

when there is labor dystocia. The IV access may be an advantage if they women augmentation with oxytocin or if something unexpected happens.

Women who are allocated to the intervention group may experience a shorter labor if the IMP has the presumed effect. In that case, they will receive less oxytocin, and experience fewer oxytocin side effects. Based on previous studies, the reduction in the active phase of labor will be approximately one hour. This reduction will take place in the first stage (opening phase), and not the second stage of labor (expulsion phase).

Based on data from our department, 72% of primiparous women who crossed the alert line (the inclusion criterion of this study) of the partogram received augmentation with oxytocin with an average duration of 214 minutes. Of the women who crossed the alert line, 15% delivered by cesarean section and 25% had an operative vaginal delivery, compared to 2% and 16% among women with normal progress in labor, respectively.

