### **Adverse events**

Adverse events will be recorded for both mother and fetus after 30 minutes after IMP is given, on the first day after delivery and at discharge from the maternity ward.

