## **7.3 Time Period for Reporting AE and SAE**

For each patient the standard time period for collecting and recording AE and SAEs will begin at start of study treatment and will continue throughout the hospital stay.

During the course of the study all AEs and SAEs will be proactively followed up for each patient; events should be followed up to resolution, unless the event is considered by the investigator to be unlikely to resolve due to the underlying disease. Every effort should be made to obtain a resolution for all events, even if the events continue after discontinuation/study completion.

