## **7.4 Recording of Adverse Events**

If the patient has experienced adverse event(s), the investigator will record the following information in the CRF:

- The nature of the event(s) will be described by the investigator in precise standard medical terminology (i.e. not necessarily the exact words used by the patient).
- The duration of the event will be described in terms of event onset date and event ended data.
- The intensity of the adverse event will be described as mild, moderate and severe.
  - Mild; asymptomatic or mild symptoms; clinical or diagnostic observations only; intervention not indicated.
  - Moderate; minimal, local or noninvasive intervention indicated; limiting age-appropriate instrumental Activities of Daily Living.
  - Severe or medically significant but not immediately life-threatening; hospitalization or prolongation of hospitalization indicated.
- Specifically, mild AEs include dryness of the mouth, transient tachycardia and flushing. Moderate AEs include visual disturbances, urinary retention, and fall in blood pressure and skin reactions. SAEs include dyspnea, anaphylactic reactions, serious skin reactions including Steven-Johnson and anaphylactic shock.
- The Causal relationship of the event to the study medication will be assessed as one of the following:

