### **9.5.5 Safety analyses**

Safety analyses are limited to descriptive statistics and tabulations.

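### The urinary retention endpoint does not require the catheter to follow IMP or to be placed for inability to void, and it closes at delivery-ward exit while adverse event recording runs to discharge

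*Protocol*

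**What the plan says.** The synopsis and section 1.7 list among the secondary endpoints: "Urinary retention, defined as need for urinary catheter before the participants leave the delivery ward (categorical variable". Section 6.1 names urinary retention again without adding to the definition.

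The same condition appears elsewhere in four roles:

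- Section 1.2 cites "post-partum urinary retention (13" as an association with oxytocin augmentation, and section 1.5 also lists retention among the side effects of oxytocin.
- Section 1.5 lists it as a side effect of butylscopolamine, of unknown frequency: "Kidney: Urinary retention". The same section puts full clearance of the drug at 24 hours.
- Section 7.4 names it as an adverse event: "Moderate AEs include visual disturbances, urinary retention, and fall in blood pressure and skin reactions".
- Section 7.3 says that adverse event collection "will begin at start of study treatment and will continue throughout the hospital stay". Section 5.2 schedules recording 30 minutes after IMP, "on the first day after delivery and at discharge from the maternity ward".

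The two records are analysed differently. Section 9.5.2 gives categorical secondary endpoints a simple two-group test, with logistic regression as a robustness check. Section 9.5.5 states: "Safety analyses are limited to descriptive statistics and tabulations".

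**The concern.** The endpoint has three gaps.

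1. **No start point.** Other labor endpoints in section 1.7 are timed from IMP; this one is not. Women are already in active labor when they become eligible, so a catheter used earlier in that labor fits the wording although the study drug cannot have caused it.
2. **No reason for the catheter.** Nothing separates inability to void from a catheter placed for a procedure. Women are included whatever their mode of delivery, and section 1.5 reports that among the department's women who crossed the alert line "15% delivered by cesarean section and 25% had an operative vaginal delivery".
3. **An early close.** Section 9.2.2 places the maternity ward on another floor from the delivery ward. Retention first recognised there cannot count in the endpoint.

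Retention could rise through the anticholinergic effect of the drug or fall through less oxytocin, so the comparison should be specific to retention. Mode of delivery is itself a post-randomization outcome. If procedural catheters count, a possible change in cesareans is mixed into the retention result. The trial could also report two retention rates, from different windows, with only one of them tested.

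**Working it through.** **Plan's own figure.** The protocol states no retention rate, catheter rate, effect size or power for this endpoint. Its only computed sample size is for the primary endpoint (section 9.1): 2 × (1.96 + 0.84)² × 2.8² / 1² ≈ 123 to 124 per arm, i.e. 246 to 248 in total, against 246 stated. That figure is reproduced and is not in question. With 250 women and 1:1 allocation, the illustration uses 125 per arm.

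**Comparing the two definitions**

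| | Endpoint (synopsis, 1.7) | Adverse event (5.2, 7.3, 7.4) |
|---|---|---|
| Start | none stated | start of study treatment |
| End | leaving the delivery ward | end of hospital stay |
| Criterion | need for a catheter | retention, no catheter required |
| Analysis | two-group test | tabulation only |

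**Inputs.** From the protocol: a cesarean share of about 7% (section 9.1, expected in the study population) or 15% (section 1.5, department data after crossing the alert line). Assumed: every cesarean involves a catheter, the cesarean share is equal in the arms, and true retention among the other women is 5% on placebo and 10% on active. None of these assumptions has a source in the protocol.

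**Formula.** Observed proportion q = b + (1 − b) × p, where b is the share with a catheter for another reason and p is true retention. The risk difference shrinks by the factor (1 − b). Approximate power = Φ((q₁ − q₀ − 1.96 × SE₀) / SE₁), where SE₀ uses the pooled proportion and SE₁ the separate ones.

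- b = 7%: 0.07 + 0.93 × 0.05 = 0.1165; 0.07 + 0.93 × 0.10 = 0.163.
- b = 15%: 0.15 + 0.85 × 0.05 = 0.1925; 0.15 + 0.85 × 0.10 = 0.235.

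| b | Placebo | Active | Risk difference | Risk ratio | Power |
|---|---|---|---|---|---|
| 0 (clean) | 5.0% | 10.0% | 5.0 points | 2.00 | 32% |
| 7% | 11.65% | 16.3% | 4.65 points | 1.40 | 18% |
| 15% | 19.25% | 23.5% | 4.25 points | 1.22 | 13% |

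With an assumed 10% vs 20%, the same steps give risk ratios of 2.0, 1.57 and 1.36, risk differences of 10.0, 9.3 and 8.5 points, and power of 60%, 44% and 32%.

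**Window.** If only half of retention shows before delivery-ward exit (assumed), 5% vs 10% becomes 2.5% vs 5.0%. The risk ratio stays at 2.0, the difference halves to 2.5 points, and power is 18% with no other catheters counted. With b = 15% as well, the risk ratio is 1.12 and power about 6%.

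**Unequal cesareans.** If cesareans were 15% on placebo and 10% on active (assumed), the active arm would read 0.10 + 0.90 × 0.10 = 19.0% against 19.25%. The distortion therefore need not be simple dilution.

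**The case against.** A reader might infer that the protocol tells staff to count every catheter. It does not. The item is headed urinary retention, and need for a catheter can fairly be read as need because of retention. No section says that women having a cesarean are catheterized. Sections 9.4 and 9.5 defer detail to a separate SAP that is not at hand, and it or the CRF may settle start and reason. This stands as a limit on the claim: counting catheters used before IMP or for a procedure is the literal reading, not a stated rule. It does not answer the closing time, which the protocol fixes itself.

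A reader might also infer that the harm is hidden. It is not. Retention on the maternity ward is recorded as an adverse event, with a start after IMP and no catheter rule, and it will be tabulated. A narrow endpoint beside a broad safety record is not in itself a contradiction. What remains is that the only tested comparison uses the shorter and less specific definition.

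The size is also open to challenge. Every retention and catheter rate is assumed. The risk ratio moves more than the risk difference, which falls only from 5.0 to 4.65 or 4.25 points. Power for 5% vs 10% is about 32% even with a clean definition, so better wording would not make the trial able to detect that doubling reliably. The case in which the difference vanishes needs a fall in cesareans that the protocol does not predict; it anticipates shorter labor and less oxytocin.

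**Conclusion.** The concern holds as a weakness in the definition. As written, the endpoint lacks a start after IMP and a reason for the catheter, and it closes before the period over which the same condition is recorded as an adverse event. Followed literally, it admits catheters the drug cannot have caused and omits later retention, which weakens the tested comparison of a listed side effect.

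The size cannot be derived from the protocol. If every cesarean involves a catheter, cesareans are equal in the arms and true retention is 5% vs 10%, the risk ratio falls from 2.0 to between 1.40 and 1.22 across the protocol's two cesarean rates, and power falls from about 32% to between 18% and 13%. The documents do not support saying that retention is lost to the trial.

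This is a minor to moderate point. Section 9.5.1 treats secondary analyses as supportive, and neither the primary analysis nor the sample size changes.

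**What to change.** In the synopsis and section 1.7, define the endpoint as catheterization for inability to empty the bladder, first needed after IMP and up to discharge from the maternity ward. State that a catheter placed only for a procedure, such as a cesarean, does not count. Add the time of and reason for catheterization to the CRF.

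Leave the adverse event in section 7.4 unrestricted. Applying the catheter-based definition there would drop retention managed without a catheter and so narrow safety recording.

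The cost is a sentence in two places and the added CRF entry. The reason must be read from the chart, where it may be poorly documented. Event counts may change in either direction: excluding procedural catheters lowers them, and the longer window raises them.
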